### Secondary outcomes

Secondary outcomes include % change in body weight, and mean change in body mass index (Kg/m^2^), blood pressure (mm Hg), haemoglobin (g/dL), fasting plasma glucose (mg/dL), total serum cholesterol (mg/dL), high-density lipoprotein (mg/dL), low-density lipoprotein (mg/dL), triglycerides (mg/dL) and urinary salt excretion (g/day).

### Intervention development

The use of theoretical models increases the likelihood for an intervention to be effective [28]. Hence, the PRECEDE-PROCEED Model (Figure 1) was used to inform the intervention [20] and the behaviour change matrix was used to guide the selection of channels and methods of communication (Table 1).

**Table 1. T0001:** Dietary behaviour change matrix.

Communication Objective	Audience	Stage of Change of the audience	Facilitating factors	Strategies*	Channels of communication	Methods of communication	Frequency of messages	Expected outcomes
To increase fruit intake	Primary Audience: Individual	Pre-contemplation	Women being main chef of the family	1. Involving family members as co-champions	1. Interpersonal communication	1. Verbal	1. SMS: weekly	1. Increase knowledge of dietary recommendations
To increase vegetable intake	(Family champion & Co-champion)		Easy availability of fruits and vegetables in the study area	2. Awareness	2. Tele-communication	2. Flip book	2. WhatsApp: weekly	2. Increase awareness about own dietary intake and benefits of SMART eating.
To reduce fat intake	Secondary Audience: Family		Accessibility to fruits and vegetables through markets and food vendors	3. Emphasis on seasonal fruits and vegetables	3. Internet	3. SMS	3. Email: weekly	3. Increase risk perception for nutrition related diseases
To reduce sugar intake				4. Visibility		4. WhatsApp: text, images & videos	4. Landline: need based	4. Increase their self-efficacy for changing dietary behaviour
To reduce salt intake				5. Good cooking practices		5. Website		5. Improve their dietary behaviour
				6. Avoidance/Substitution		6. e-mail		6. Increase the purchase of fruits and vegetables and reduce their monthly consumption of fat, sugar and salt
				7. Emphasis on sharing		7. Educational aids: Dining table mat, Kitchen calendar and pamphlets		
				8. Building self-efficacy		8. Measuring spoons (5g)		
				9. Emphasis on cutting down on medical bills				
				10. Kitchen gardening if feasible				

*Details regarding strategies are available in the text of the article

Taking into account the available literature on nutrition education interventions, the National Institute of Nutrition dietary guidelines, and findings from the formative research (Supplementary file 1), the contents of the nutrition education program were prepared [29]. This included the health benefits of eating more fruits and vegetables and reducing consumption of fat, sugar and salt; dietary guidelines, pictorial portion guides (for estimating the amount of fruits and vegetables that should be consumed in a day); the importance of using a measuring teaspoon (for estimating the use of fat/oil, sugar and salt); tips to increase fruit and vegetable intake and to reduce fat, sugar and salt intake; body mass index; frequently asked questions and a quiz on fat, sugar, salt, and fruit and vegetables. A SMART eating kit has been prepared which includes several educational aids such as a dining tablemat, kitchen calendar and measuring spoons. A SMART eating flip book has also been prepared. The IT intervention includes the SMART eating website development with an interactive help function, short message service (SMS) applications in the form of text, videos and images and e-mail. A nutrition education pamphlet has also been prepared for the control group.

All intervention tools were designed by the first author (JK). Content validation was done by eight experts from related fields in PGIMER, Chandigarh. The website design was finalised by two co-authors and one nutrition expert. The tools were pre-tested on five health professionals and 15 families from different socio-economic groups (5 families each of LIG, MIG and HIG) and modifications were made.

### Intervention components

The nutrition education intervention will have two components (Table 2). The *Interpersonal Component* includes: home visits for training of family champions and co-champions using a flip book over a period of one month; distribution of the SMART Eating kit with written information in Hindi language; and health check-up reports (lipid profile, haemoglobin and fasting plasma glucose etc.) after the baseline survey. *Information Technology (IT) Component* will be implemented, after training of family champions, through mobile phone, landline phone and internet communications.

**Table 2. T0002:** Description of intervention components.

Intervention components			Duration	Description
1	Interpersonal component			
	a	Training of family champions and co-champions	1 month	Face-to-face training will be provided using flip book on how to use different features of the intervention on internet and mobile phones or tablets.
	b	Distribution of SMART Eating kit		Kit containing innovative educational aids in the form of a dining table mat, kitchen calendar and spoons will be provided to all families.
		A dining table mat		A laminated dining table mat on dietary recommendations for fat, sugar, salt, fruits and vegetables, one side of which will guide the families on vegetables and fruits available in summer and winter season, how much and when to eat. The other side of the mat will remind family members of consuming less oil, sugar and salt by reducing the intake of foods high in fat, sugar and salt.
		Kitchen calendar		A pictorial kitchen calendar for display in the kitchen to remind family members of using less fat, sugar and salt while cooking.
		Measuring spoons		A set of three measuring spoons will be provided to help families measure the amount of fat, sugar and salt they use.
	c	Tailored nutrition education		Nutrition education will be tailored to the specific needs of family members e.g. those already suffering from diabetes and high blood pressure and those at high risk of developing these chronic conditions such as family history of diabetes, hypertension and obesity etc.
	d	Health check-up		Blood test reports of lipid profile, haemoglobin and plasma glucose will be delivered at their door steps for motivating them to modify their dietary behaviour.
2	Information technology component			
	a	Tele-communication		
		SMS	6 months	SMS will be sent weekly in Hindi language
		WhatsApp		WhatsApp messages will be sent weekly in English, Hindi and Punjabi.
		Landline		Landline phone will be used to take feedback from family members if anyone do not reply to mobile phone call
	b	Internet		
		SMART Eating website	6 months	SMART Eating website available in three languages (English, Hindi and Punjabi) will be password protected to prevent spill-over effect. Each family will be provided with individual password to login. Password will be sent through SMS, WhatsApp and email.
		Content delivery		Content will be delivered in parts. New content will be added every fortnightly.
		Using content on website		Content will be used by the participants on their own
		Query box for interactive help		Interactive help will be provided through query box or e-mail for any time assistance to discuss any difficulties in using the intervention or adherence to dietary changes. Through this participants can drop their questions in the query box at any time and responses will be given by the experts in the field of nutrition. In addition, query box will have provision for discussion among the participants.
		● Quiz and frequently asked questions (FAQs)		Quiz on fat, sugar, salt, vegetables and fruits and FAQs

### Intervention implementation

The intervention will be implemented at a family level using the family champion approach – an adaptation of health champion approach [30] – and the ‘Empowerment approach’ to build capacity of the individuals and families [31]. The family champion approach will motivate all other family members to eat less fat, sugar and salt and consume more fruit and vegetables. The multi-channel communication approach includes interpersonal communication, tele-communication (mobile phone) and internet (website). The same intervention will be delivered to all intervention families. Clear instructions for families not to share intervention messages with other families or friends in the study area will be given.

Intervention implementation strategies will include:
*Involvement of family members*: especially children as co-champions with a view to increasing self-efficacy for dietary changes.
*Creating awareness*: by providing information on nutrition.
*An emphasis on seasonal fruits and vegetables*: which are less expensive at their peak season, and are full of nutrients.
*Increasing visibility*: by placing a tray containing fruits and vegetables on the dining room or kitchen table, and keeping snacks and food items high in fat, sugar and salt in places less visible to family members.
*Highlighting good cooking practices*: such as methods requiring less fat, sugar and salt.
*Avoidance and substitution*: avoiding food too high in fat, sugar and salt or substituting snacks with fruits and vegetables.
*Emphasis on eating by sharing*: fruits and vegetables among family members whatever the amount available.
*Building self-efficacy*: SMART eating kit articles to increase the self-efficacy in changing dietary behaviour.
*Cutting down on the medical bills*: emphasising the benefits of increasing fruits and vegetables and decreasing fat, sugar and salt to prevent chronic diseases which in turn may help to reduce medical bills.
*Kitchen gardening*: Encouraging, if feasible, kitchen gardening or growing vegetables in earthen pots.

### Intervention in the control group

Control group families will be provided with a pictorial pamphlet on dietary recommendations from the National Institute of Nutrition, India. The content and pictures in the pamphlet will be the same as that used for the dining table mat to be provided to intervention group families. One side will have information on seasonal fruits and vegetables along with dietary recommendations; the other side will have pictures of measuring spoons showing the amount of salt, sugar and fat in one spoon; dietary recommendations; pictures of foods high in fat, sugar and salt; and information on reducing the intake of these nutrients. The pamphlet will be in Hindi and will be provided to study participants along with their blood test reports. Participants will be asked to read the information provided in the pamphlet in their own time, to make changes to their diet accordingly and to convey the same information to their family members.

### Data collection

The following tools have been developed for data collection: (1) Household profile proforma to identify Index case; (2) Structured Questionnaire for Index case: Part A – Socio-demographic data, medical history and physical measurements, Part B – ‘Stages of change’ questions based on those developed by Lechner *et al* (1998) to assess participant’s self-rated dietary intake [32] and Part C – Attitude, social influence and self-efficacy questions based on ‘Attitude-Social influence-(self)-efficacy model’ (ASE model) using a five point Likert scale [33]; (3) Proforma for selecting family champion and co-champion; (4) Information technology use proforma; (5) A validated Food Frequency Questionnaire (FFQ) for individual dietary assessment [34]; (6) Household food purchase and consumption record proforma to assess food consumption at household level [34]; (7) Sphygmomanometer, weighing scale, anthropometric rod, and laboratory equipment for collecting blood and urine samples; and (8) Feedback proforma.

Height will be measured to the nearest 0.1 cm using the anthropometric rod. Weight will be measured with minimum clothing without shoes to the nearest 0.1 kg on a portable electronic weighing scale. Blood pressure will be measured twice using a standard instrument to the nearest 2 mm Hg [35]. Blood samples (5 mL: 1 mL-EDTA vial, 1 mL-Oxalate vial and 3 mL-plain vial) will be obtained to estimate haemoglobin, plasma glucose (mg/dL), total serum cholesterol (mg/dL), high-density lipoprotein (mg/dL), low-density lipoprotein (mg/dL) and triglycerides (mg/dL) using standard laboratory methods. Instructions regarding overnight (12 hrs.) fasting will be given to all participants one day prior to blood sample collection [36]. Morning fasting urine samples (5 mL) will be collected in urine containers. Participants with blood pressure above 140/90 mm Hg in both intervention and control groups and those with abnormal blood test results will be referred to doctors in the local health centre.

After implementing the intervention for a period of one month, all participants will be invited, through a SMS, phone call or home visit, to ask whether they have made some changes to their diets. For process evaluation, feedback will also be taken from the participants using a proforma. A log book will be maintained to record barriers and enablers related to the use of the IT-enabled intervention as well as identifying actions that could be taken to improve its use. Qualitative in-depth interviews using ‘Extreme or Deviant case’ sampling will also be conducted to understand barriers and facilitators.

A team of three members, the first author and two other members who are outsiders to the community, will collect the data. The team members have received training on data collection. Neither the investigator nor the data collectors will be blind to intervention. Intervention implementation, process evaluation, and quality control will be conducted by the first author.

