## Abstract

Nutrition is an important determinant of health. At present, nutrition programs in India mainly emphasize improving maternal and child nutrition. Adult nutrition has not received due attention, though diseases like hypertension and diabetes are largely preventable through changes in dietary and physical activity behaviour. Little is known about the best approaches to improve dietary behaviours, especially the role of modern information technology (IT) in health education. We describe the protocol of the SMART Eating (Small, Measurable and Achievable dietary changes by Reducing fat, sugar and salt consumption and Trying different fruits and vegetables) health promotion intervention. A Cluster Randomised Controlled Trial will evaluate the effect of an IT-enabled intervention on nutrition behaviour among urban adults of Chandigarh, India. Formative research using a qualitative exploratory approach was undertaken to inform the intervention. The IT-enabled intervention programme includes website development, Short Message Service (SMS), e-mail reminders and interactive help by mobile and landline phones. The IT-enabled intervention will be compared to the traditional nutrition education program of distributing pamphlets in the control group. The primary outcome will be the percentage of study participants meeting the dietary intake guidelines of the National Institute of Nutrition, Hyderabad, India and the change in intake of fat, sugar, salt, fruit and vegetables after the intervention. The difference in differences method will be used to determine the net change in dietary intakes resulting from the interventions. Measurements will be made at baseline and at 6 months post-intervention, using a food frequency questionnaire. The formative research led to the development of a comprehensive intervention, focusing on five dietary components and using multi-channel communication approach including the use of IT to target urban North Indians from diverse socio-economic backgrounds. The Cluster Randomised Controlled Trial design is suitable for evaluating the effectiveness of this IT-enabled intervention for dietary behaviour change.

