### Sampling

A multi-level sampling strategy will be used. Twelve clusters, based on the type of housing (LIG, MIG and HIG), have been selected bearing in mind that there is sufficient geographic separation to avoid any spill-over effect of the intervention. Similar clusters will be paired together to form six pairs. For each of the six pairs, computer generated randomisation will be used to allocate clusters to intervention and control groups by a researcher not involved in the study. The number of clusters and cluster size will be fixed. Equal numbers of families will be recruited from each cluster through systematic random sampling. One adult (35–70 years) per family will be randomly selected as the index case for the baseline and post-intervention assessment.

One family champion (the adult member who cooks food most of the time) will be selected from each family for the implementation of the intervention. In recognition of the fact that not all family champions will be using information technology tools or mobile phones (as demonstrated through the formative research), one co-champion will also be selected from each family. A co-champion can be any person from the family identified by the family champion who would be able to assist him/her in using the internet and mobile phone communications.

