### Data analysis

The quantitative data analysis will be performed using Statistical Package for Social Sciences (SPSS) version 21 based on Intention-to-treat analysis. The cluster design will be taken into consideration during analysis and cluster effect will be reported. Descriptive statistical analysis will include calculation of sample means, standard deviation (SD) and proportions according to the type of variables. Categorical variables will be compared using chi-square test. Within group changes in quantitative variables from baseline to endline at six months will be analysed using a paired *t*-test. Unpaired *t*-tests will be applied to independent samples for between group comparisons. In order to explore potential differences between groups (e.g. socio-economic, age groups and gender etc.) multivariable regression analysis will also be used.

The FFQ data will be entered into the spreadsheet software used in the PURE study [34]. This software determines the amount of food (from the food list) consumed by the individual, by multiplying the average consumption with frequency of intake and portion size of the food item. The intake of each food item will then be re-computed for a day, and then multiplied with the nutrient amount per gram to obtain the daily nutrient intake from each food. The estimated nutrient intakes per day will then be summed to obtain the total daily nutrient intakes.

Participants’ nutrient intakes per day will be compared against the NIN dietary guidelines to calculate the percentage of participants meeting the guidelines for fat, sugar, salt, fruit and vegetable intake. Sub-group analysis by disease status will also be performed. Changes in fat, sugar, salt, fruit and vegetable intake in both the groups will be calculated as post-intervention minus pre-intervention nutrient intakes. The net intervention effect will be calculated as the change in dietary intake in the intervention arm minus the change in dietary intake in the control arm from baseline to the study end at six months (difference in differences method) [37]. Dietary information collected through food purchase and consumption records will also be used to calculate the change in per capita monthly consumption of fat, sugar, salt and fruit and vegetables for each family. The clinical significance of changes achieved will be estimated based on association of nutrient intakes with clinical outcomes reported in existing literature.

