### Methodological considerations

Considering the potential risk of non-use of IT components by the families, process evaluation will be undertaken to assess the extent of various intervention components and identify factors hindering the use of IT-enabled intervention. In case participants do not make sufficient use of IT components, we may plan to continue the intervention by distributing printed materials.

That said, the ability to measure any changes in dietary intake will require robust assessment measures. FFQs have emerged as a useful tool in epidemiological studies across the world, and these have become popular in Indian settings because they impose fewer burden on the subjects compared to other dietary assessment methods. Our FFQ has been developed and validated in a northern Indian setting [34]. The dietary intake of the index case was considered to be representative of the family. At family level, fat, sugar, salt, and fruit and vegetable intake will also be assessed through self-reported purchase which can be used to triangulate findings from FFQ.

Assessment of salt intake from FFQs usually underestimates the intake so urinary sodium assessment provides better information [61]. Though 24-hour urinary sodium excretion is gold standard for estimating salt intake [62], there is some evidence to show that spot urine samples can be used to estimate mean change in population salt intake, and, as this poses much less of a burden to participants, and the equations to estimate 24 hour salt from spot urine samples have been previously tested in different Indian populations; our assessment is based on single spot urine samples [63]

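### The person who delivers the intervention is also one of three unblinded collectors of a self-reported primary outcome; this overlap is avoidable, and the order of allocation and recruitment should be stated

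*Protocol article*

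**What the plan says.** On who measures, the Data collection section of the protocol article states: "A team of three members, the first author and two other members who are outsiders to the community, will collect the data". It adds: "Neither the investigator nor the data collectors will be blind to intervention". On who delivers, the same section says: "Intervention implementation, process evaluation, and quality control will be conducted by the first author".

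On what is measured, the Abstract says: "Measurements will be made at baseline and at 6 months post-intervention, using a food frequency questionnaire". The Data analysis section turns FFQ responses into daily nutrient intakes, and then: "Participants’ nutrient intakes per day will be compared against the NIN dietary guidelines to calculate the percentage of participants meeting the guidelines". For salt, Methodological considerations points elsewhere: "our assessment is based on single spot urine samples". Urinary salt excretion is listed under Secondary outcomes.

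On entry to the trial, the Sampling section pairs twelve clusters into six pairs and says that "computer generated randomisation will be used to allocate clusters to intervention and control groups by a researcher not involved in the study". The next steps described are a fixed number and size of clusters, and then: "Equal numbers of families will be recruited from each cluster through systematic random sampling". One adult per family is drawn at random as index case. Families that do not consent are excluded. No sentence says whether consent and baseline come before or after the allocation is known.

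Strengths and limitations accepts that the absence of blinding calls for cautious interpretation. It does not mention that deliverer and assessor overlap.

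**The concern.** Participants and the deliverer cannot be blinded in a trial of this kind. Who records the outcome is a separate choice. Here a person with a direct stake in the programme, who implements it and checks the quality of the data, also collects part of the outcome data, and the other two collectors know the allocation as well.

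The outcome is open to influence from both sides. A participant may give answers that please, and a collector may probe or record portions differently. Intervention families have a month of home visits and six months of messages, while control families have a pamphlet. A pull towards favourable answers may therefore be stronger in one arm. If it is, it looks like an intervention effect, and a larger sample does not reduce it.

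A second, smaller matter concerns entry. If allocation were known when families are approached, consent and baseline answers could differ by arm. The article does not say which comes first.

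**Working it through.** **1. Does the planned analysis remove a reporting shift?** Write the reported change in each arm as true change plus change in reporting error, b:

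- Net effect = (true_I + b_I) − (true_C + b_C) = (true_I − true_C) + (b_I − b_C).

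Error that is the same at baseline and endline cancels within an arm (b = 0). Error that arises after the intervention equally in both arms also cancels. A shift that arises afterwards in one arm more than the other does not.

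**2. Which components have an objective check?** Salt has spot urine. Fat, sugar, fruit and vegetables have none: the household purchase record offered for triangulation is itself self-reported. Blood tests, weight and blood pressure are secondary outcomes and do not measure these intakes.

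**3. The plan's sample size.** The inputs in the Sample size section are 15% in control, a 20-point gain to 35%, significance level 0.05 (two-sided assumed) and power 0.80.

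- Uncorrected: n = [1.96·√(2·0.25·0.75) + 0.8416·√(0.15·0.85 + 0.35·0.65)]² / 0.20² = 72.4, so 73.
- With continuity correction: (72.4/4)·[1 + √(1 + 4/(72.4·0.20))]² = 82.1, so 83, as stated.
- Then 83 × 2 = 166; 166 × 1.10 = 182.6, so 183; 183 × 2 = 366 per arm and 732 in total.

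The plan's figure reproduces. The point here does not depend on it except for scale and workload.

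**4. Illustration of scale (the bias is assumed; the documents give none).** Take no true effect, 15% meeting the guideline in control, and 366 × 0.9 = 329.4 analysed per arm. With design effect 2 this is 164.7 effective per arm. The test is a two-proportion normal comparison at endline, two-sided 0.05. With differential over-report d:

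- SE under the null: √(2·p̄(1−p̄)/164.7). SE at the biased values: √([p₁(1−p₁) + p₂(1−p₂)]/164.7).
- d = 5 points (15% against 20%): SEs 0.0419 and 0.0418; Φ[(0.05 − 1.96·0.0419)/0.0418] plus a negligible other tail = 0.22.
- d = 10 points (15% against 25%): SEs 0.0441 and 0.0437; Φ[(0.10 − 1.96·0.0441)/0.0437] = 0.62.

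| Assumed d across the arm | False positives, design effect 2 | Design effect 1 |
|---|---|---|
| 0 | 5% | 5% |
| 2 points | 8% | 11% |
| 5 points | 22% | 39% |
| 10 points | 62% | 90% |

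**5. How much of that belongs to the overlap?** If the first author does a share s of endline interviews and these carry an extra shift e in the intervention arm only, the arm-wide bias is s × e. The share is not given. With an equal split (assumed), s = 244/732 = 1/3, so a 5-point arm-wide bias from this source alone needs a 15-point shift in those interviews. The table therefore shows what differential reporting from any source could do, not what the overlap alone would do.

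**6. Workload under the fix.**

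- Without dropout: 732/3 = 244 endline visits each for three collectors; 732/2 = 366 each for two.
- After 10% dropout: 732 × 0.9 ≈ 659; 659/3 ≈ 220 and 659/2 ≈ 329.
- Either way 3/2 = 1.5, so 50% more per remaining collector.

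**The case against.** Several objections have force.

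- The limitation is disclosed. That is true of non-blinding in general. The overlap of roles is not mentioned there, and unlike participant blinding it can be avoided.
- The first author is one of three collectors, the split of interviews is unknown, and the article does not say how the FFQ is administered. This stands, and it means that bias may enter, not that it does.
- A reader might infer that participants report to the person who taught them. The documents do not support this. Intervention components and Table 2 direct face-to-face training to family champions and co-champions, while outcomes come from a randomly drawn index adult who need not be either.
- A reader might also infer that families are recruited after allocation. Only the order of sentences in Sampling suggests it. No time word says so, and the design figure, which may show the sequence, is not available. Systematic sampling, random choice of the index adult and an independent allocator would in any case leave mainly differential consent and baseline reporting, and stable baseline differences are offset by the difference in differences.
- Control families receive the same dietary content in a pamphlet with their blood reports, and are asked to change their diet. They too may report favourably, and only the difference between arms matters. This may shrink the bias, but nothing shows that it cancels.
- Masking may fail, because intervention homes hold a kitchen calendar and a table mat. Taking the deliverer out of endline assessment still helps if masking fails.

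**Conclusion.** The point holds in a limited form. The article itself states that the deliverer and quality controller is one of three unblinded collectors of a primary outcome that rests on self-report. The general caveat does not cover this, the analysis would not remove a differential shift that arises after the intervention, and an objective check exists for salt only.

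The size is unknown. The false-positive figures rest on an assumed over-report, a 15% control rate, a simple endline comparison and the plan's own design effect. On the guideline-adherence scale the true size would also depend on how many participants lie near each cut-off. On timing, the finding is only that the order of allocation, consent and baseline is not stated and can easily be fixed. The point does not invalidate the trial; it is an improvement worth making before endline and, where still possible, before recruitment.

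**What to change.** In Data collection, assign all endline FFQ, blood pressure and anthropometry to the two outside collectors. Each should cover both clusters of a pair, so that collector differences do not align with arm, and should not be told the allocation where that is feasible. State that the person delivering the intervention collects no endline outcome.

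In Sampling, state the order of steps: the independent researcher discloses a pair's allocation only after consent and baseline are complete in both of its clusters.

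Neither change alters the sample size or the intervention, and no one needs to be added to the team. The cost is about half as many endline visits again for each of the two collectors (244 to 366, or about 220 to 329 after 10% dropout), which may lengthen the endline round. Kit items on display in homes will unmask some visits.
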